## Abstract

Supplemental Digital Content is available in the text

## Introduction

1

Current fertility rates are well below those needed for a population replacement rate of 2.1 in most Organization for European Economy Cooperation (OECD) countries; however, South Korea in particular has the lowest fertility rate among all the OECD countries.^[1]^ The high infertility rate of the country is thought to be partially attributable to social factors such as the increase in the number of working couples, marriage age, stressors, and environmental pollution.^[2]^ While the government increasingly supports infertility treatments, such as in vitro fertilization (IVF), the fertility rate remains low.^[3]^

Ovulation disorders (prevalence rate, 15%) and tubal and intra-abdominal abnormalities (prevalence rate, 30–40%) are thought to be the causes of female infertility, but other causes are unknown in Western medicine.^[4]^ Patients with degraded ovarian function comprise 9% to 24% of all infertility patients, and the pregnancy rate after IVF and embryo transfer is as low as 30% to 40%.^[5]^ The largest obstacle in increasing the overall pregnancy rate is the low post-IVF pregnancy rate in patients with aggravated ovarian function who show a weak response to controlled ovarian hyperstimulation.^[6]^ Despite the many proposed ovulation induction methods for the low response group, no clinically significant differences have been reported.^[7]^ In addition, indiscreet assisted reproductive technology in Western medicine causes infertility patients to have a decreased quality of life and to incur high costs; moreover, artificial ovulation induction results in various side effects. Patients have been looking for complementary options to improve fertility.

Korean medicine (KM) has become very common as a primary or adjuvant therapy method for infertile patients^[3]^ and has been reported to improve IVF success rates.^[8]^ Approximately 60% of infertile patients had used KM treatment before using assisted reproductive technology in 2012.^[3]^ A study showed that KM improved ovarian quality; however, no regimen is available for infertility patients with deterioration of ovarian function.^[9]^ One systematic review reported that acupuncture and herbal medicine treatments had significantly improved ovarian function compared with Western medicine treatments for patients with deterioration of ovarian function.^[10]^ However, few studies have investigated the effects of KM for improving ovarian function in patients with deteriorating ovarian function. Therefore, we will perform a prospective multicenter observational study that reflects actual clinical practices including the interventions applied to patients and progress status.

## Participants and methods

2

### Study aims

2.1

The aim of this study is to investigate the effects of KM on poor ovarian reserve (POR) in infertility patients.

### Study design/setting

2.2

This study is a prospective multicenter observational study. We will recruit patients from the You & Green Korean Medical Clinic in 4 regions (Daejeon, Busan, Daegu, Sejong) (Fig. 1). Data collection and follow-up schedules are shown in Table 1.

**Figure 1 F1:**
[figure not shown]
A flowchart of the study. AEs = adverse events, AMH = anti-Mullerian hormone, E2 = estradiol, EQ-5D = European Quality of Life-5 Dimensions, FSH = follicle-stimulating hormone, KM = Korean medicine, LH = luteinizing hormone, QoL = quality of life, POR = poor ovarian reserve.

**Table 1 T1:**
[figure not shown]
Schedule of study visits and assessments.

### Study registration

2.3

This study is registered with the Clinical Research Information Service (https://cris.nih.go.kr/cris/en/): KCT0004209. Current protocol version is 1.1.

### Eligibility criteria

2.4

#### Inclusion criteria

2.4.1

We will include patients who are eligible according to the following criteria:

1.Females between 25 and 44 years of age who have been diagnosed with infertility.2.Those without a history of surgical procedures but with an antral follicle count (AFC) < 4 or an anti-Müllerian hormone (AMH) level < 1.0 ng/mL in both ovaries confirmed through ultrasonographic examination.3.Those with a history of surgical procedures but with an AFC < 4 or an AMH level < 1.0 ng/mL in both ovaries confirmed using ultrasonography.^[11]^4.Failure to achieve a clinical pregnancy after 12 months or more (6 months for females aged 35 and above) of regular unprotected sexual intercourse.^[12]^5.Written informed consent to participate in the study.6.Compliance with the study regulations.

#### Exclusion criteria

2.4.2

1.Those with an irregular menstrual cycle of less than 21 days or more than 40 days.2.Those who take antidepressants, anti-serotonin, antipsychotics, or other anti-psychiatric drugs.3.Those who received hormone therapy within 6 months.4.Those who participated in other clinical trials within the past 6 months.

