### Recruitment

2.5

We will recruit 50 female patients with infertility at the You & Green Korean Medical Clinic. The researcher will explain the aim of this study and the details of the procedures and will obtain informed consent from potential subjects prior to the collection of information. Participants will be free to withdraw at any time during the study, and this will not affect their clinical treatment.

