#### Secondary outcome

2.7.2

Ovarian function testing: Ovarian function testing will be assessed with luteinizing hormone, follicle-stimulating hormone, estradiol, and AMH testing^[13]^ before and after the 3 months of KM treatments. Blood tests will be performed on the 2nd or 3rd day after the menstrual period.

Adverse events: All participants will be required to report any adverse events (AEs) when they occur during the trial at every visit. Each AE will be recorded in the case report form (CRF) by the site investigator and will be assessed for causality.

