### Sample size calculation

2.9

Preliminary studies of prospective observational studies require more than 12 participants.^[14,15]^ We calculated the number of patients needed considering the percentage of eligible patients who visit You & Green Korean Medicine Clinic on typical days; the estimated sample size was 40 participants. We will recruit 50 patients considering the dropout rate of 20%.

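### Entry has washouts for hormone therapy and other trials but none for Korean medicine (KM), so women already under KM can be enrolled and the sole comparator, their own baseline, may not be untreated

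*Protocol article*

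**What the plan says.** Section 2.4.2 (Exclusion criteria) is a numbered list of four items: cycle irregularity, "Those who take antidepressants, anti-serotonin, antipsychotics, or other anti-psychiatric drugs", "Those who received hormone therapy within 6 months", and "Those who participated in other clinical trials within the past 6 months". Section 2.4.1 (Inclusion criteria) has six items: age and infertility diagnosis, two on ovarian reserve, failure to conceive, consent and compliance. Neither list mentions earlier or current KM, a KM washout, or a restriction to new KM patients.

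The patients come from the clinics that give the study treatment. Section 2.2 states "We will recruit patients from the You & Green Korean Medical Clinic in 4 regions", and section 2.5 states "We will recruit 50 female patients with infertility at the You & Green Korean Medical Clinic". The sample size in section 2.9 was set "considering the percentage of eligible patients who visit You & Green Korean Medicine Clinic on typical days", with no limit to first visits. Under section 2.6 the study treatment is those clinics' own usual KM.

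Ovarian function is measured "before and after the 3 months of KM treatments" (section 2.7.2). Section 2.10 gives McNemar, paired t or Wilcoxon signed rank tests for the outcomes. No control group is described. The Introduction adds that "Approximately 60% of infertile patients had used KM treatment before using assisted reproductive technology in 2012".

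**The concern.** Section 2.1 sets out to study the effects of KM on poor ovarian reserve. With paired tests and no control group, each woman's baseline is the only thing her later value is compared with. For the change to represent the effect of 3 months of KM, that baseline should not already carry KM effects.

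The authors did fence off two exposures that could disturb the baseline, hormone therapy and other trials, but not the exposure being evaluated. A site applying the printed lists has no ground to refuse a woman who is in the middle of a course of the clinic's own treatment. For her, the 3 study months are a continuation. This reaches the primary outcomes in section 2.7.1 (the symptom questionnaire and quality of life) as well as the hormone tests, because symptoms may already have moved before entry.

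There is a safety side too. Women still under KM at recruitment have tolerated it so far, and those who stopped because of adverse events are less likely to be at the clinic to be enrolled. Adverse events may therefore be under-counted.

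**Working it through.** **1. The plan's own figure.** Section 2.9: 40 evaluable women and 20% dropout. 40 / (1 − 0.20) = 50, which reproduces the stated target. No significance level, power, effect size or standard deviation is given, so there is no power figure to reproduce.

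**2. The rule applied to a case.** Take a woman aged 35 who meets the ovarian reserve and infertility criteria, has a regular cycle, takes no psychiatric drugs, has had no hormone therapy and no other trial in the past 6 months, and has been on the clinic's KM for some time. She meets all six inclusion criteria and none of the four exclusions. She is eligible.

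**3. Size of the dilution.** Let f be the share of analysed women with recent or ongoing KM, and g the fraction of the 3-month effect already present in them at entry. If the others show the full change, the measured mean change relative to the true one is

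(1 − f) + f × (1 − g) = 1 − f × g.

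The documents give neither f nor g. Both are assumed here. With f = 20%:

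- g = 25%: 0.20 × 0.25 = 5% dilution
- g = 50%: 0.20 × 0.50 = 10%
- g = 100%: 0.20 × 1.00 = 20%

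**4. What that means with 40 completers.** This is an illustration with an assumed two-sided 5% paired t test (exact noncentral t) and the standard deviation of the change held fixed. With n = 40, 80% power needs a standardized paired change of about 0.45. If that is the true change in women without earlier KM, power becomes:

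| Share pre-treated, f | g = 50% | g = 100% |
|---|---|---|
| 10% | 76% | 71% |
| 20% | 71% | 61% |
| 30% | 66% | 50% |

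**5. Direction.** The formula allows only dilution. If the pre-treated women at the clinics are mainly those who respond to or tolerate KM, their further change could be larger than average, and the bias could run the other way. The table is a scale for one mechanism, not an estimate for this study.

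**The case against.** The strongest defence is that the study is meant to reflect routine practice, and open entry suits that purpose. Sections 2.6 and 2.7.2 can also be read as describing a course that starts after the baseline test, and section 2.5 puts consent before any data collection. These points make routine enrolment of women in mid-course less certain. They do not bar it: a baseline test before the study months can still fall within an earlier course. A routine-practice design explains the free choice of KM treatments, but it does not make a treated baseline untreated, and the authors already restrict entry for other exposures.

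Figure 1 and Table 1 are not shown, and an article may leave treatment history to the case report form and subgroup reporting to the analysis plan. This stands: neither recording of earlier KM nor a separate analysis can be called missing. The point therefore rests on the eligibility rule, which is printed as finished lists.

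A reader might take the Introduction's 60% and infer that most participants will be pre-treated. The documents do not support that. The figure concerns any KM use before assisted reproduction in 2012, among infertile patients generally. It is not recent or ongoing use at these clinics and cannot stand in for f.

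It is also fair that an exclusion could cost more than a slight delay if earlier KM is common, and that nothing in the documents supports a particular length of KM washout.

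**Conclusion.** The point holds as a fault in a stated eligibility rule. Women already under KM can be enrolled, their baseline may be taken on treatment, and the before-after change may then not measure the effect of 3 months of KM. With no control group and no restriction at entry, the paired tests in section 2.10 cannot by themselves separate the two kinds of patient.

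The size is unknown because the documents do not show the share pre-treated. Under the assumed f = 20% and g = 25% to 100%, the dilution is 5% to 20%. Dilution is the likelier direction, but selection of responders or tolerators could offset or reverse it.

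Two stronger conclusions are tempting and should not be drawn. One is that the baseline of every outcome is contaminated. That depends on how many pre-treated women actually enter, which could be few. The other is that the adverse event rate will be too low. Under-counting is a risk that follows from selecting women who tolerate KM, not something the documents show.

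**What to change.** Add to section 2.4.2 an exclusion for KM treatment for infertility or gynecological symptoms within a pre-specified window. The 6 months already used for hormone therapy is one candidate, and the investigators should confirm the length. State that all baseline measurements are taken before the first KM treatment of the current episode.

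If exclusion would slow recruitment too much, record the date of last KM at baseline and report the before-after change and the adverse events separately for women with and without recent KM. The group without recent KM should carry the conclusion about the effect of KM.

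Cost: one eligibility line or one baseline question. The target of 50 does not change under exclusion, but more otherwise eligible women must be approached, 50 / (1 − f). At an assumed f = 20% that is 50 / 0.80 = 62.5, so 63. Under the second option the main analysis set shrinks to 40 × (1 − f), or 40 × 0.80 = 32 at the same f. The real cost depends on the unknown share with recent KM, which the clinics could check from their own patient flow before choosing.

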### Recruitment

2.5

We will recruit 50 female patients with infertility at the You & Green Korean Medical Clinic. The researcher will explain the aim of this study and the details of the procedures and will obtain informed consent from potential subjects prior to the collection of information. Participants will be free to withdraw at any time during the study, and this will not affect their clinical treatment.

### Intervention

2.6

The participants will be treated for 3 months with the standard protocol practiced at the You & Green Korean Medical Clinics. KM interventions (herbal medicine, acupuncture, electroacupuncture, herbal acupuncture, auricular acupuncture, moxibustion, manual therapy, etc) will be prescribed for infertility treatment in the same manner as in actual clinical practice, without the limitation of the number of interventional treatments. Herbal medicine will be prescribed according to individual symptoms and pattern identification. The detailed herbal prescriptions according to pattern identification are listed in Table 2. The dosages and contents of the herbs will be the same as that used in actual clinical practice. If necessary, acupuncture or another KM will be prescribed once a week. If the patient becomes pregnant during treatment, these treatments will be stopped.

**Table 2 T2:**
[figure not shown]
KM herbal prescription for KM diagnosis.

### Outcomes measures

2.7

#### Primary outcome

2.7.1

KM clinical symptoms questionnaire for pattern identification in gynecology: This questionnaire was developed for diagnosis pattern identification and measuring the clinical symptoms of KM. The questionnaire consists of 44 clinical items measured with a 5-point Likert score (from 1 [none] to 5 [very severe]).

Quality of life: We will use the Korean version of the European Quality of Life-5 Dimensions questionnaire, which has been well validated.

#### Secondary outcome

2.7.2

Ovarian function testing: Ovarian function testing will be assessed with luteinizing hormone, follicle-stimulating hormone, estradiol, and AMH testing^[13]^ before and after the 3 months of KM treatments. Blood tests will be performed on the 2nd or 3rd day after the menstrual period.

Adverse events: All participants will be required to report any adverse events (AEs) when they occur during the trial at every visit. Each AE will be recorded in the case report form (CRF) by the site investigator and will be assessed for causality.

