### Statistical analysis

2.10

We will analyze categorical and continuous variables with McNemar test and a paired *t* test (in the case of a nonnormal distribution, the Wilcoxon signed rank test will be used), respectively. We will also perform a Chi-squared test or a Fisher exact test for AE rates, the rates of AEs that cause dropout, and the rated of severe AEs.

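### As written, the hormone blood draw is counted after the menstrual period rather than from its first day, which adds avoidable within-woman timing noise to the before-after changes in FSH, LH and E2

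*Protocol article*

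**What the plan says.** Section 2.7.2 (Secondary outcome) of the protocol article lists ovarian function testing by "luteinizing hormone, follicle-stimulating hormone, estradiol, and AMH testing", measured "before and after the 3 months of KM treatments". It then gives the timing rule: "Blood tests will be performed on the 2nd or 3rd day after the menstrual period". No other text in the article ties the draw to the first day of bleeding or to a numbered cycle day. Table 1 (visit schedule) and Figure 1 (flowchart) are not reproduced in the copy reviewed.

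Three other places bear on the point:

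- Section 2.2 describes the design: "This study is a prospective multicenter observational study". Recruitment is from clinics in four regions, and under section 2.6 every participant is treated, so there is no control group.
- Section 2.10 plans a paired analysis: "We will analyze categorical and continuous variables with McNemar test and a paired" *t* test, with the Wilcoxon signed rank test as the nonnormal alternative. No cycle-day term is mentioned.
- Section 2.4.2 excludes "Those with an irregular menstrual cycle of less than 21 days or more than 40 days", so cycles of 21 to 40 days are admitted.

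**The concern.** FSH, LH and E2 move through the menstrual cycle, so a before-after change is interpretable only if both samples come from about the same point in it. A count that begins at the end of bleeding makes the sampling day depend on how long bleeding lasts, and that can differ between two cycles three months apart. The paired test then attributes to treatment whatever part of the change comes from the shift in cycle day.

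The hormones are secondary outcomes, but the stated aim in section 2.1 is the effect of Korean medicine on poor ovarian reserve, and they are the only listed outcomes that measure ovarian function. Three of the four depend on the sampling day; AMH is less exposed. The primary outcomes, a symptom questionnaire and a quality-of-life scale, do not depend on this rule.

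**Working it through.** **The plan's own figure.** Section 2.9 says "the estimated sample size was 40 participants", and allows 20% dropout: 40 / (1 − 0.20) = 50, the stated recruitment target. This reproduces, and the timing point does not change it. The 40 is a feasibility count and was not derived from any hormone effect.

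**Cycle day of the draw.** Let day 1 be the first day of bleeding and *L* the length of bleeding in days. Under the rule as written, cycle day = *L* + 2 or *L* + 3. The article gives no value for *L*, so these are assumptions:

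| Assumed *L* | Cycle day of draw |
|---|---|
| 3 | 5 or 6 |
| 5 | 7 or 8 |
| 7 | 9 or 10 |

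Counted from onset, the draw is on cycle day 2 or 3 for every woman at both assessments. The spread from day 5 to day 10 is a spread *between* women and largely cancels in a paired comparison.

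**Within-woman shift.** This is what pairing does not remove. If *L* differs by 1 to 3 days between a woman's two sampled cycles (assumed), the rule moves her second draw by the same 1 to 3 days. The free choice between the two permitted days can add up to 1 day, giving 2 to 4 at most, but that extra day would remain under the onset rule too.

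As a standard deviation, let *s* be the within-woman SD of bleeding length. Suppose each permitted day is equally likely, which contributes a variance of 0.25 per draw. With two independent draws:

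SD of shift = √[2 × (*s*² + 0.25)]

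| Assumed *s* (days) | SD of shift, rule as written |
|---|---|
| 0.5 | √(2 × 0.50) = 1.0 |
| 1.0 | √(2 × 1.25) = 1.6 |
| 1.5 | √(2 × 2.50) = 2.2 |

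Counted from onset, *s* drops out: √(2 × 0.25) = 0.7 days.

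**Illustration on the outcome scale.** The article gives no hormone change per cycle day, so the effect on FSH, LH or E2 cannot be computed. As an illustration only, 40 pairs give 80% power (two-sided 5%, normal approximation) for a mean change of (1.96 + 0.84) / √40 = 0.44 SD. If timing added a fraction *f* to the variance of the change, power would be Φ[2.80 / √(1 + *f*) − 1.96]. For assumed *f* of 10%, 25% and 50% this is about 76%, 71% and 63%.

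**The case against.** The strongest reply is that the sentence is a slip. Naming two specific days suggests days 2 and 3 of the cycle, and the article never says that counting starts at the end of bleeding. With Table 1 and Figure 1 not shown, the intended anchor cannot be confirmed. This stands as a limit on certainty: if the clinics count from onset, the problem is confined to the wording. It does not make the wording sound, because this is the only timing rule the article gives to clinics in four regions.

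A reader might also infer more than the document supports:

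- *That differences in sampling day between women distort the result.* The planned test is paired, so stable differences in bleeding length largely cancel.
- *That the hormone changes are biased.* Bias needs bleeding length to move systematically between the two assessments, and nothing in the article shows that it will. Without such a movement the consequence is noise. If it did occur, for instance through treatment, there would be no control group with which to separate it.
- *That admitting cycles of 21 to 40 days makes the draw day vary more.* Cycle length does not enter the formula. It changes only the relative phase: day 10 is about 48% of a 21-day cycle (10/21) and 25% of a 40-day cycle (10/40). The mid-cycle case combines the shortest admitted cycle, the longest assumed bleeding and the later permitted day.

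Finally, a cycle-day field on the case report form and a sensitivity analysis may well sit in the full protocol or analysis plan. Their absence from the article is not a fault.

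**Conclusion.** The point holds in limited form. The article states a specific sampling rule that, taken literally, ties the draw to the end of bleeding, and on the kindest reading leaves the anchor unclear. Followed as written, it raises the SD of the within-woman shift in cycle day from 0.7 days to between 1.0 and 2.2 days, for an assumed within-woman SD of bleeding length of 0.5 to 1.5 days. The effect on FSH, LH and E2 themselves is unquantified, and the power figures rest on assumed variance fractions. The established consequence is added noise in three secondary outcomes. The claim that the planned comparison *is* confounded by cycle timing goes beyond the document. The correction is still worth making, because these hormones are the study's only measures of ovarian function and the change costs very little.

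**What to change.** In section 2.7.2, reword the rule so that blood is drawn on day 2 or 3 counted from the first day of menstrual bleeding, at both assessments, and check that Table 1 says the same.

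Optionally, record the actual cycle day of each draw on the case report form, so that FSH, LH and E2 pairs with a sample outside the window can be examined in a sensitivity analysis.

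The cost is one phrase and, if the option is taken, one form field. No visit or blood draw is added and the sample size does not change. If the clinics already count from onset, practice stays as it is and only the text is corrected.
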